### Eligibility criteria

Patients with NAFLD who will be recruited in this study must satisfy the inclusion and exclusion criteria presented in Tables 1 and 2. Fatty liver, steatosis grade and fibrosis stage will be assessed using noninvasive methods (ultrasound, vibration-controlled transient elastography (VCTE), and magnetic resonance imaging (MRI)).

**Table 1 Tab1:** Efficacy and safety of PERIOdontal treatment versus usual care for Nonalcoholic liver disease (PERION) inclusion criteria

Criteria type	Description of inclusion criteria
Sex and age	Men and women: 20–85 years of age
Diet and exercise therapy	Patients with NAFLD who did not respond to 3-month diet and exercise therapy
ALT levels	Patients with an ALT level of > 40 IU/L at the start of this study
Fatty liver	Patients with a diagnosis of fatty liver based on abdominal ultrasonography^a^
Steatosis grade	Patients with the equivalent of steatosis grade ≥ 1 on CAP (using FibroScan) and/or PDFF (using MRI)^b^
Fibrosis stage	Patients with the equivalent of fibrosis stage < 4 on TE (FibroScan) and/or MRE^c^
Alcohol consumption	Patients with no habitual alcohol consumption (i.e., consumption of ethanol > 30 g/day in men and > 20 g/day in women)
Periodontitis	Patients with chronic moderate periodontitis (holding rate of periodontal pocket depth of > 4 mm is > 10 sites)
Other	Patients who can provide written consent to participate in this research in person, follow instructions during participation in this research, undergo protocol-specified physical examination and other examinations, and report symptoms or events

*ALT* alanine aminotransferase, *CAP* controlled attenuation parameter, *MRE* magnetic resonance elastography, *MRI* magnetic resonance imaging, *NAFLD* nonalcoholic fatty liver disease, *PERION* PERIOdontal treatment for NAFLD, *PDFF* proton density fat fraction, *VCTE* vibration-controlled transient elastography. ^a^Criteria of fatty liver, as defined by the existence of hepatorenal echo contrast. ^b^Defined by CAP ≥ 236 dB/m and/or PDFF ≥ 5.2%. ^c^Defined by VCTE < 14 kPa and/or MRE < 6.7 kPa

**Table 2 Tab2:** Efficacy and safety of PERIOdontal treatment versus usual care for Nonalcoholic liver disease (PERION) exclusion criteria

Criteria type	Description of exclusion criteria
Liver comorbidity	Patients with any other concurrent liver disease, such as hepatitis C, hepatitis B, or autoimmune hepatitis
	Patients with drug-induced symptomatic NAFLD
Other comorbidity	Patients with concurrent or past history of any serious cardiac, vascular, hematological, respiratory, hepatic, renal, gastrointestinal, or neuropsychiatric disease
	Patients with a history of abdominal or gastrointestinal surgery, except appendicitis
Medication	Patients with any change to their orally administered medications within 3 months before informed consent
	Patients with diabetes mellitus being treated with insulin injections
Other	Patients who have participated in any other clinical study and received study treatment within 1 month before the start of this research (counted from the first day of study medication)
	Breastfeeding women or women with possible pregnancy
	Other patients who are inappropriate as participants in this research in the opinion of the principal investigator, etc.

*NAFLD* nonalcoholic fatty liver disease, PERION PERIOdontal treatment for NAFLD

### Randomization

Before providing informed consent, patients will undergo a screening test as a first step to determine whether they meet the inclusion criteria for the study and none of the exclusion criteria. For patients determined to be eligible, the principal investigator or co-investigator will complete a Patient Enrollment Form with the necessary information, which is sent by fax or e-mail to the Patient Enrollment Center (Yokohama City University). The Patient Enrollment Center will then confirm the eligibility of the patient based on the enrollment form, enroll and randomize the patient, and notify the principal investigator or co-investigator of the Patient ID number and the allocation number via fax or e-mail. After an eligibility check, patients will be randomly assigned to receive periodontal treatment or no treatment at the Central Registration Center by a computer program, using a stratified block randomization method, adjusting for age (≥ 65/< 65 years) and sex (male/female). Therefore, the patient assignment is concealed from the investigator.

### Study procedures

The schedule of assessments for the study procedures is summarized in Table 3.

**Table 3 Tab3:** Objectives and procedures of the Efficacy and safety of PERIOdontal treatment versus usual care for Nonalcoholic liver disease (PERION) study

	Study time point (weeks)					
	Screening period	Treatment period				Follow-up period
Study objectives	− 4	0	4	8	12	60
**Primary objective**						
Change in ALT levels from baseline	○	○			○	○
**Key secondary objective**						
Change in serum IgG antibody titer for *P. gingivalis*	○				○	○
**Other secondary objectives**						
Change in blood endotoxin activity by EAA	○	○	○	○	○	○
Change in liver fat content using CAP and MRI-PDFF	○	○			○	
Change in liver stiffness using VCTE and MRE	○	○			○	
Change in oral bacterial counts using NGS and qPCR	○	○			○	
Change in blood parameters for liver function (AST, GTT, ALP, and T-Bil)	○	○	○	○	○	○
Change in blood lipid parameters (T-Cho, LDL-C, TG, and HDL-C)	○	○	○	○	○	○
Change in blood parameters related with inflammation in NAFLD (ferritin, CK-18, TNF-α, IL-6, and h-CRP)		○			○	
Change in blood parameters related with fibrotic marker in NAFLD (type IV collagen 7S)		○			○	
Change in blood diabetic factors (blood glucose, insulin, and HOMA-IR)		○	○	○	○	○
Change in BMI	○	○	○	○	○	○
Assessment of periodontal treatment safety		○	○	○	○	○
Dropout ratio in each group		○	○	○	○	○
**Tertiary objectives**						
Change in blood parameters for renal function (BUN, Cr, eGFR)	○	○	○	○	○	○
Change in HRQOL using SF-8™	○	○			○	○

All objectives will be compared between the periodontal scaling and root-planing treatment group and the tooth-brushing treatment group. *ALP* alkaline phosphatase, *ALT* alanine transaminase, *AST* aspartate transaminase, *BMI* body mass index, *BUN* blood urea nitrogen, *CAP* controlled attenuation parameter, *CK-18* cytokeratin 18, *Cr* creatinine, *EAA* endotoxin activity assay, *eGFR* estimated glomerular filtration rate, *FBS* fasting blood sugar, *GGT* γ-glutamyltransferase, *h-CRP* high-sensitivity C-reactive protein, *HDL-C* high-density lipoprotein-cholesterol, *HOMA-IR* homeostasis model assessment of insulin resistance, *HRQOL* health-related quality of life, *IL-6* interleukin-6, *LDL-C* low-density lipoprotein-cholesterol, *MRE* magnetic resonance elastography, *MRI* magnetic resonance imaging, *NAFLD* nonalcoholic fatty liver disease, *NGS* next-generation sequencer; PERION, PERIOdontal treatment for NAFLD, *PDFF* proton density fat fraction, *qPCR* quantitative polymerase chain reaction, *SF-8* short form-8, *T-Bil* total bilirubin, *T-Cho* total cholesterol, *TG* triglycerides, *TNF-α* tumor necrosis factor-α

#### Observation of adverse events

All adverse events (AEs) during the study will be recorded with regard to the following: date of onset and date of completion (if applicable), severity of AEs, investigator’s view on the relationship to periodontal treatment, information on actions taken, information on the treatment of the AE, the cause of the event (if known), and the solution or outcome. AEs classified as serious will be recorded in the serious adverse event reporting tool and reported to the sponsor. AE intensities are graded according to the National Cancer Institute’s Adverse Event Common Terminology (NCI CTCAE) version 4.03, including the AE-intensity classifications shown in Table 4.

**Table 4 Tab4:** Classifications of adverse event (AE) intensity

Grade	Description
Grade 1 (mild)	Asymptomatic or mild symptoms; clinical or diagnostic observations only; intervention not indicated
Grade 2 (moderate)	Minimal, local, or noninvasive intervention indicated; limiting age-appropriate instrumental ADL
Grade 3 (severe)	Medically significant but not immediately life-threatening; hospitalization or prolongation of hospitalization indicated; disabling; limiting self-care ADL
Grade 4 (life-threatening)	Life-threatening consequences; urgent intervention indicated
Grade 5 (death)	Death related to AE

*ADL* activities of daily living, *AE* adverse event

#### Additional study procedures

Patients must be fasted for at least 8 h prior to the visit. The study visits will be at 0, 4, 8, 12, and 60 weeks.

#### Criteria for discontinuation of study treatment

The study must be discontinued under the following conditions: drug-induced liver injury, unacceptable toxicity, acute viral hepatitis B and C, autoimmune or alcoholic hepatitis, hypoxic or ischemic liver injury, biliary tract disease, or pregnancy.

### Outcome measures

#### Evaluation of efficacy

The efficacy endpoints for this study are shown in Fig. 3.

#### Evaluation of safety

The safety and tolerability of periodontal treatment will be evaluated over the 60 weeks of treatment in NAFLD patients with periodontitis. This will include the evaluation of AEs, clinical laboratory tests, physical examination, and vital signs. The clinical laboratory tests will include liver and fasting metabolic parameters. Liver parameters will include alkaline phosphatase (ALP), AST, ALT, total bilirubin (T-Bil), and γ-glutamyltransferase (GGT).

### Statistical analyses

The Full Analysis Set (FAS) will be the primary analysis set for efficacy. We define FAS to include any subjects who receive any amount of the study medication without a lack of information on the primary endpoint (complete case analysis). For the blood liver function test using ALT, the summary statistics (mean, standard deviation) will be calculated at baseline and 12 weeks. Details of the statistical design will be described in the Statistical Analysis Plan. In this study, statistical analysis will be performed mainly for the following items. For the primary analysis, (ALT after treatment – ALT at baseline) will be sought for each subject and the corresponding Wilcoxon test will be performed. The significance level will be 5% on both sides. In addition to *p* values, we will provide point estimates with 95% confidence intervals. As a sensitivity analysis, the two groups would be compared using the analysis of covariance using the primary endpoint as an outcome, adjusting for ALT at baseline as a covariate. For the key secondary endpoint, *P. gingivalis* IgG antibody titer in the blood (values after treatment – values at baseline) will be sought for each subject and the paired Wilcoxon test will be performed. Subgroup analysis will be conducted. Stratified analysis will be performed using *P. gingivalis* bacterial content, proton density fat fraction (PDFF), magnetic resonance elastography (MRE), and periodontal pocket as indices. Stratified analysis will be performed using above/below the median of *P. gingivalis* bacterial content, endotoxin, PDFF, MRE, and periodontal pocket depth. We hypotheses a larger reduction in ALT with the intervention in the patient group with high *P. gingivalis* bacterial content, high endotoxin levels, high PDFF, low MRE, and deep periodontal pockets at baseline. Therefore, we conducted multivariable linear regression with difference in ALT between groups as dependent variable and at least the treatment group, the respective subgroup variable (categorized), and the interaction term (treatment group×subgroup variable) as independent variables. The significance level will be 5% on both sides. In addition to p values, we will provide point estimates with 95% confidence intervals. As a sensitivity analysis, the two groups will be compared using analysis of covariance using the key secondary endpoint as an outcome adjusting for *P. gingivalis* IgG antibody titer at baseline as a covariate. As the safety analysis, the incidence and severity of AEs and reactions will be calculated.

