### Sample size determination

Our previous pilot study showed that nonsurgical periodontal treatments on 10 NAFLD patients for 3 months ameliorated the liver function parameters, such as the serum levels of AST and ALT [15]. It showed a mean ALT change of − 25.0 (IU/L), with a standard deviation of 25. On the basis of these data, the sample size is determined to guarantee the power of the analysis of variance *F* test. Assuming the mean changes in ALT in the no-treatment group and active treatment groups to be 0 and − 25, respectively, with a common standard deviation of 25, the required number of patients per group with a power of 80% and a two-sided significance level of 5% was calculated to be 16. We aim to recruit a total of 40 patients (scaling and root-planing treatment, 20, tooth-brushing treatment, 20) to compensate for the dropout patients.

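### The primary ALT test is an unadjusted Wilcoxon on change (about 75% power if it compares the arms), while the baseline-adjusted between-group ANCOVA is only a sensitivity analysis

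*Protocol article*

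**What the plan says.** In the protocol article, Statistical analyses, the primary analysis takes each patient's post-treatment ALT minus baseline ALT; this difference "will be sought for each subject and the corresponding Wilcoxon test will be performed". No covariate is named. The word corresponding does not settle whether this is a rank-sum test between arms or a signed-rank test within arms. The parallel sentence for the *P. gingivalis* IgG titer reads "will be sought for each subject and the paired Wilcoxon test will be performed", which by name is a test of change within patients.

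The analysis that expressly compares the arms ranks below this: "As a sensitivity analysis, the two groups would be compared using the analysis of covariance using the primary endpoint as an outcome". The only covariate listed for it is baseline ALT. IgG has the same order, with an ANCOVA on baseline titer as the sensitivity analysis.

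The Randomization section allocates patients "using a stratified block randomization method, adjusting for age" (65 years and over, or under 65) and sex. Neither factor is listed in either main ALT analysis.

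Sample size determination rests on an F test: "the sample size is determined to guarantee the power of the analysis of variance". Mean changes of 0 and −25 IU/L and a common SD of 25 are assumed, and the number per group "with a power of 80% and a two-sided significance level of 5% was calculated to be 16". Forty patients are to be recruited and 32 are expected to have outcome data. Further statistical detail is referred to a statistical analysis plan that is not shown.

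**The concern.** Patients enter on an ALT threshold of about 40 IU/L, so regression to the mean is likely: a higher baseline goes with a larger fall. With 16 evaluable patients per arm, a chance difference in baseline ALT passes straight into an unadjusted comparison of changes. The plan already contains the model that removes this, but ranks it second. The trial was also sized for an F test and is to be analysed with a rank test, so the stated power does not belong to the stated primary test. At this sample size, lost power is hard to recover.

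The wording adds a separate risk. If the primary test is read as paired, like the IgG test, it does not estimate the difference between arms at all.

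**Working it through.** **Inputs.** From Sample size determination: difference 25 IU/L, SD of change 25, two-sided 5%, power 80%, 16 per arm. The correlation ρ between baseline and 12-week ALT is not given. It is an assumption here, shown from 0.3 to 0.9, with equal variances at the two times and the SD of change held at 25.

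**The plan's own figure.** n per arm = 2(1.960 + 0.842)² × 25²/25² = 15.7, so 16. The stated figure reproduces by the normal approximation (power 80.7% at 16). With the exact t distribution (with two groups, the F test) power is 78.1% at 16 and 80.7% at 17.

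**Rank-sum test on change.** Under normal errors its efficiency relative to the t test is 3/π = 0.955, so 80% power needs about 17/0.955 = 17.8, that is 18 per arm. Simulation at 16 per arm gives about 75% power at every ρ.

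**ANCOVA.** If each ALT value has variance σ², the change has variance 2σ²(1 − ρ) and the residual after baseline adjustment has σ²(1 − ρ²). The ratio is (1 + ρ)/2, so the residual SD is 25√((1 + ρ)/2). Power at 16 per arm under normal errors:

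| ρ | Residual SD | ANCOVA, formula (29 df) | ANCOVA, simulated | ANCOVA with age and sex, if not prognostic | Rank test on baseline-adjusted residuals | Rank-sum on change |
|---|---|---|---|---|---|---|
| 0.3 | 20.16 | 92.4% | 92% | 90% | 90% | about 75% |
| 0.5 | 21.65 | 88.4% | 87% | 85% | 85% | about 75% |
| 0.7 | 23.05 | 84.3% | 83% | 79% | 80% | about 75% |
| 0.9 | 24.37 | 80.1% | 79% | 76% | 75% | about 75% |

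The formula runs slightly high because it ignores chance baseline imbalance.

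**Non-normal errors, raw scale, ρ = 0.3, 0.5, 0.7, 0.9.**
- Log-normal follow-up errors: Wilcoxon on change 87.6%, 90.3%, 93.0%, 94.5%; ANCOVA 89.2%, 88.1%, 84.0%, 81.3%.
- Heavy tails (t, 3 df): Wilcoxon 85.9%, 88.2%, 90.1%, 92.4%; ANCOVA 92.0%, 89.3%, 86.0%, 84.5%.
- Stronger skew: Wilcoxon 91%, 94%, 97%, 98%; rank test on baseline-adjusted residuals 99%, 99%, 98%, 98%.

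**Log-normal ALT above 40 IU/L at entry, assumed 30% reduction, ρ = 0.3, 0.5, 0.7.** Wilcoxon on raw change 36%, 47%, 67%; log-scale ANCOVA 60%, 68%, 84%. Wilcoxon on the log ratio (separate run; baseline median 70 and log SD 0.45 assumed) gives 46%, 60%, 79%. So the log scale alone supplies about 46 − 36 = 10 of 24 points, 60 − 47 = 13 of 21, and 79 − 67 = 12 of 17. Adjustment supplies the rest.

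**Type I error.** Simulated without strata at ρ = 0.6: rank-sum 4.1%, ANCOVA 4.9%.

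**The case against.** A pre-specified between-group rank test on change is valid, keeps its type I error, and is a reasonable choice for 32 patients and a laboratory enzyme selected above a threshold. The adjusted comparison is already planned and will be reported. The analysis plan, not shown, may add covariates. All of this stands, and it makes the point one of efficiency and clarity. It does not remove the point, because the article itself fixes the primary test and its rank.

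A reader might infer that the unadjusted Wilcoxon always wastes precision. It does not: with skewed or heavy-tailed errors it beats raw-scale ANCOVA at moderate to high correlation. That advantage comes from using ranks, not from leaving baseline out, since the rank test on adjusted residuals keeps it.

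A reader might also infer that omitting age and sex biases the result or has a known cost. Omission is conservative at most. The article gives no figure linking either factor to ALT change, so the cost cannot be computed.

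Nor does sizing on an F test imply ANCOVA. With two groups that test is the unadjusted t test on change. It shows a mismatch between sizing and analysis, and no more.

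**Conclusion.** The point holds in this limited form. If the primary test compares the arms and errors are roughly normal, its power at 16 per arm is about 75%, against a stated 80%. Moving the baseline-adjusted ANCOVA up would give about 92% to 79% over correlations of 0.3 to 0.9. The gain is large at low correlation and small near 0.9. With age and sex added but not prognostic, little is left at 0.9 (76%). Every gain rests on an assumed correlation.

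The log-normal comparison also favours adjustment, but it should not be read as the effect of adjustment alone, because part of that gap is the change of scale.

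The article does not establish that the primary test is within-arm; it leaves this open. The power figures above apply only to the between-group reading. Under the paired reading the defect would be more serious, because no between-group primary test would be stated.

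**What to change.** Before any unblinded analysis:

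1. Make a between-group ANCOVA the primary analysis, with arm, baseline ALT, age stratum and sex as terms.
2. Fix one scale in advance: change in IU/L, which keeps the stated endpoint, or log ALT if skew is expected. The log scale changes the reported effect to a ratio, so the endpoint wording must then change too.
3. Keep a rank test as the sensitivity analysis, state that it compares the arms, and apply it to baseline-adjusted residuals.
4. For IgG, replace the paired test with a between-group ANCOVA on the baseline titer. Table 3 schedules one pre-treatment IgG sample, at week −4, so that is the baseline.

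This mainly reorders analyses already planned and adds two covariates the trial already holds. It costs a few degrees of freedom and about 2 to 3 points of power if age and sex are not prognostic. Raw-scale ANCOVA is also more sensitive to outlying ALT values, which is the reason to keep the rank analysis beside it.

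### The key secondary endpoint (P. gingivalis IgG) is given a within-patient Wilcoxon test that does not compare the randomised arms, and the primary ALT test is worded so that it could be read the same way

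*Protocol article*

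**What the plan says.** All the analysis sentences are in the Statistical analyses section of the protocol article.

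- **Key secondary endpoint (IgG titer).** The change from baseline "will be sought for each subject and the paired Wilcoxon test will be performed". The sentence names no arms.
- **Primary endpoint (ALT).** The change from baseline "will be sought for each subject and the corresponding Wilcoxon test will be performed". The sentence names neither the arms nor the type of Wilcoxon test.
- **Sensitivity analysis, primary.** "As a sensitivity analysis, the two groups would be compared using the analysis of covariance using the primary endpoint as an outcome", with baseline ALT as covariate.
- **Sensitivity analysis, key secondary.** "the two groups will be compared using analysis of covariance using the key secondary endpoint as an outcome", with baseline titer as covariate.

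Other parts of the article describe a comparison of arms. The footnote to Table 3 states: "All objectives will be compared between the periodontal scaling and root-planing treatment group and the tooth-brushing treatment group". The Design section sets one group against the other. Under Sample size determination, "the sample size is determined to guarantee the power of the analysis of variance" *F* test.

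**The concern.** A paired Wilcoxon (signed-rank) test on after-minus-baseline values has as its null hypothesis that the changes are centred on zero. Treatment allocation does not enter it. Run within an arm, it gives one p value per arm and none for the difference. Run on all patients together, it averages over the arms. Neither version answers the randomised question.

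Within-patient change also absorbs anything the arms share, and the article describes several candidates:

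- Lifestyle advice is offered without distinction by arm (NAFLD treatment).
- Brushing instruction appears to come before scaling (Periodontal treatment), so the scaling arm's change would include the comparator's effect.
- ALT has an entry threshold of 40 IU/L (Table 1), which invites regression to the mean in ALT.
- IgG is scheduled at week −4 and not at week 0 (Table 3), so its change spans the period before treatment.

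For IgG, the main p value would therefore not support a claim about periodontal treatment against usual care. For ALT, the wording leaves open which of two quite different p values is the primary result, in a trial the article acknowledges is open-label.

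**Working it through.** **Step 1. Which test does the sample size belong to?** The inputs are from Sample size determination: "Assuming the mean changes in ALT in the no-treatment group and active treatment groups to be 0 and − 25, respectively". The SD of the change is taken as 25 IU/L in each arm, power as 80% and the two-sided level as 5%. The stated result is 16 per group.

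- Two arms, normal approximation: n = 2 × (1.960 + 0.842)² × (25/25)² = 2 × 7.85 = 15.7, so 16 per group. This reproduces the plan. Power at 16 is Φ(√(16/2) − 1.960) = Φ(0.868) = 80.7%.
- Two arms, exact *t*/*F* test: 16.7, so 17 per group. Power at 16 is 78.1%.
- One sample or paired, same inputs: n = (1.960 + 0.842)² × (25/25)² = 7.85, so 8.

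The figure of 16 comes from a two-arm comparison. A paired calculation would have given half as many.

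**Step 2. Set the sentences side by side.**

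| Place | What it implies |
|---|---|
| Table 3 footnote | Between arms, all objectives |
| Design | Between arms |
| Sample size determination | Between arms (*F* test) |
| IgG main test | Within patient (stated) |
| ALT main test | Not specified |
| ANCOVA, both endpoints | Between arms, sensitivity only |

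The IgG row conflicts with the first two rows. The ALT row is open. Its sentence runs parallel to the IgG one and reserves mention of the two groups for the sensitivity analysis, which favours a paired reading. The first three rows favour a rank-sum test on the changes.

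**Step 3. What would a paired test do if the arms did not differ?** This was simulated for ALT: normal changes, SD 25, 16 per arm, 6,000 runs, two-sided 5%, and the same mean change in both arms. The shared change is an assumption; the article gives no figure for it.

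| Shared fall (IU/L) | Paired, one arm (n = 16) | Paired, pooled (n = 32) | Rank-sum between arms |
|---|---|---|---|
| 0 | about 4% | about 5% | about 4.5% |
| 5 | about 11% | about 20% | about 4.6% |
| 10 | about 29% | about 57% | about 4.9% |
| 15 | about 57% | about 89% | about 4.4% |

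The between-arm test holds its level whatever the arms share. The paired test does not.

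**Step 4. Power of a rank-sum test.** Under the plan's own assumptions (0 against −25, SD 25, 16 per arm), the simulated power is 74.8%, about 75%. The simulation error is about √(0.75 × 0.25/6,000) = 0.6 percentage points, so the shortfall from 80% is not noise.

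**Step 5. IgG.** The article gives no SD, expected effect or expected drift for the titer. Steps 3 and 4 cannot be repeated for it. The objection to the IgG test rests on what the test compares, not on a rate.

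**The case against.** The strongest reply has four parts.

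1. **A reader might infer that the primary endpoint is also tested with a paired test. The article does not say so.** The word *paired* appears only in the IgG sentence. A rank-sum test on per-patient changes fits *corresponding* just as well, and the Design section, the sample size and the Table 3 footnote all point to it. A sensitivity analysis would also normally address the same question as the main one. This stands: the primary is ambiguous, not stated as paired.

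2. **A reader might infer that the plan has no between-arm inference. It has.** Both endpoints have a baseline-adjusted ANCOVA between arms, and the subgroup regression for ALT contains a treatment term. This stands too. The defect is which analysis is called the main one.

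3. **The simulated rates concern ALT, and the larger ones need large drifts.** This stands. At shared falls of 1, 3 and 6 IU/L, the paired test in 16 patients rejects in about 5%, 6% and 13% of trials (6%, 10% and 25% for 32 pooled). Nothing in the article supports a drift of 10 to 15 IU/L. Patients had already failed three months of diet and exercise. If ALT eligibility is judged at screening and baseline is week 0, regression to the mean could be small. Selection on ALT also says little about IgG.

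4. **Details may be left to the Statistical Analysis Plan.** This helps the primary, where the type of test is unstated. It does not help IgG, where the article names a specific test that conflicts with its own footnote.

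**Conclusion.** For the key secondary endpoint the plan is wrong as written. The named test assesses change from baseline, contradicts the Table 3 footnote, and leaves the only overall comparison of arms as a sensitivity analysis. This conclusion depends on no assumed figure.

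For the primary endpoint the test is not adequately fixed. A between-arm test is probably intended, since 16 per group follows from a two-arm calculation, but a paired reading remains plausible. The sentence needs clarifying; it is not evidence that the primary analysis ignores randomisation.

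The rates of about 11%, 29% and 57% show how a paired ALT test would behave under assumed shared falls of 5, 10 and 15 IU/L with normal changes and SD 25. They are not estimates of this trial's false-positive rate and do not carry over to IgG. Nor does the article say that significance in one arm alone would be taken as efficacy.

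If the primary is a rank-sum test, its power is about 75% at 16 per arm under the plan's assumptions, below the stated 80%.

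**What to change.** - Make the between-arm ANCOVA adjusted for baseline, already specified for both endpoints, the main analysis of the 12-week ALT and IgG changes. It is also the closer match to the *F* test used for sizing. Its exact power cannot be given here because the article states no baseline-to-12-week correlation.
- If a rank test is preferred, name it as the two-sample Wilcoxon rank-sum test on the 12-week changes, with the Hodges-Lehmann difference between arms and its 95% confidence interval. Keep ANCOVA as the sensitivity analysis. For the primary, restate the power as about 75% at 16 per arm, or revise the number needed.
- Label any paired within-arm test as descriptive, and state that no efficacy conclusion rests on it.

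The cost is one sentence per endpoint in the protocol and the matching text in the Statistical Analysis Plan, plus a line on power if rank-sum is kept. No new data are needed. The change should be dated and made before the arms are compared.
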